## 12 quality management and assurance

The study is being conducted in accordance with the ICH-GCP guidelines. The mandatory consultation was carried out by the QA Unit on May 17, 2024, with a certificate dated July 15, 2024. The sponsorship authorization required in this context according to the specifications of the Charité QA Unit was granted to the study director on July 22, 2024 by the Dean of the Charité - Universitätsmedizin [name]. [name].

### 12.1 Standard Operating Procedures (SOPs)

The study is based on quality management with SOPs in accordance with the study implementation under professional law, which specifies the necessary processes for carrying out the tasks of the study management or sponsor tasks and in particular for sponsor oversight .

### 12.2 monitoring

According to ICH-GCP, monitoring (study supervision) should ensure that

- (a) 'the rights and well-being of the subjects are protected.
- (b) the study data reported are accurate, complete and verifiable using source documents.
- (c) the study is conducted in accordance with the currently approved protocol/amendments, good clinical practice and applicable regulatory requirements." (ICH-GCP, 5.18.1)

As part of the risk assessment, the risk of adverse events and risks to the rights and well-being of the trial subjects were assessed as very low. However, due to the limited prior experience of the trial centers, risks of errors in study documentation and deviations from the protocol by the trial centers were considered to be quite possible. According to ADAMON, we therefore decided on a risk-adapted approach at level K2 (33) .

In summary, monitoring consists of central monitoring (Central) and on-site monitoring (On Site). In addition, monitoring is carried out by the study coordination, an independent special monitor and co-monitoring by the Clinical Trials Office (CTO) of the Charité. The exact procedure is described in the SocPres\_Monitoringplan .

|                                  |                                   |                                                                                                         |                  |
|----------------------------------|-----------------------------------|---------------------------------------------------------------------------------------------------------|------------------|
| Version: V1.2                    | Last review:
February 12, 2025 | Created: [name], [name], [name], [name], [name] | Page
40 of 52 |
|                                  |                                   | Reviewed by: [name], [name]                                                    |                  |
| Release on:
February 12, 2025 | Next check:
N/A                | Released: [name]                                                                       |                  |
|                                  |                                   | Valid from: 04.09.2024                                                                                  |                  |

|                   |                          |                                                                 |  |
|-------------------|--------------------------|-----------------------------------------------------------------|--|
| study
protocol | Study: „Soziales Rezept“ | Campus:
CCM                                                  |  |
|                   |                          | Scope:
Institute for General Practice and
Family Medicine |  |

## 13 Security

### 13.1 Adverse events

In the literature on social Prescribing does not describe any adverse events associated with the intervention. However, to demonstrate safety, a comprehensive monitoring procedure will be established in accordance with ICH-GCP , which will consist of short-term reporting of individual case reports, periodic reports, safety monitoring by an independent committee (DSMB, see below) and a comprehensive safety analysis of the study.

#### 13.1.1 definition of adverse events

Since this is another study according to Section 15 of the Professional Code of Conduct for Doctors with a complex intervention without a drug or medical device, a classification of adverse events according to Common Terminology Criteria for Adverse Events (CTCAE) v5.0. Instead, the following adverse events are predefined for the study:

1) Death (any cause)

2) Emergency room visit (any cause)

Visit an emergency room. The report should be made regardless of whether the person is subsequently admitted to hospital or not.

3) Unplanned hospitalization (any cause)

An unplanned hospitalization is characterized by a hospital admission without a prior appointment.

4) Suicide attempt/suicidality

A suicide attempt is defined as a self-performed, harmful behavior with the intention of causing death, but which does not result in death (ICD-11: MB23.R, ICPC-3: PD14).

In this context, suicidality is understood as thoughts, ideas or ruminations about the possibility of ending one's own life, ranging from the consideration that one would be better off dead to the formulation of elaborate plans (ICD-11: MB26.A, ICPC-3: PS05).

5) Other relevant adverse events

|                                  |                                   |                                                                                                         |                  |
|----------------------------------|-----------------------------------|---------------------------------------------------------------------------------------------------------|------------------|
| Version: V1.2                    | Last review:
February 12, 2025 | Created: [name], [name], [name], [name], [name] | Page
41 of 52 |
|                                  |                                   | Reviewed by: [name], [name]                                                    |                  |
| Release on:
February 12, 2025 | Next check:
N/A                | Released: [name]
Valid from: 04.09.2024                                             |                  |

|                   |                          |                                                                 |  |
|-------------------|--------------------------|-----------------------------------------------------------------|--|
| study
protocol | Study: „Soziales Rezept“ | Campus:
CCM                                                  |  |
|                   |                          | Scope:
Institute for General Practice and
Family Medicine |  |

To give investigators the opportunity to report further adverse events that they consider relevant, there is a separate category.

### 13.1.2 reporting of adverse events

Adverse events are reported using the form *SocPres\_ReportingFormEvents* via secure communication channels by the investigators to the study management within 7 days of becoming known. The exact procedure is specified in the *SOP SocPres\_SOP : Reporting, evaluation and handling of adverse events*.

### 13.1.3 Central documentation of adverse events

All adverse events are recorded centrally by the study management in a database: *SocPres\_LineListing* and tracked until the final evaluation.

### 13.1.4 second assessment of adverse events

The secondary assessment of adverse events is carried out using the form *SocPres\_EvaluationFormEvents* by the study management within 7 days of submission by the investigators. The procedure is defined in the *SOP SocPres\_SOP Reporting, assessment and handling of adverse events*.

## 13.2 reporting

After recruitment of 50 patients each, or at least every three months, a safety report with the reported adverse events is prepared and submitted to the DSMB.

## 13.3 Data Safety Monitoring Board (DSMB)

The objectives of the DSMB are

- protecting the interests of study participants,
- the evaluation of the safety and effectiveness of the intervention during the study and
- monitoring the implementation of the study.

The DSMB receives and reviews information on the progress and data generated during the study.

This includes:

1. the assessment of data quality, including completeness,

|                                  |                                   |                                                                                                         |                  |
|----------------------------------|-----------------------------------|---------------------------------------------------------------------------------------------------------|------------------|
| Version: V1.2                    | Last review:
February 12, 2025 | Created: [name], [name], [name], [name], [name] | Page
42 of 52 |
|                                  |                                   | Reviewed by: [name], [name]                                                    |                  |
| Release on:
February 12, 2025 | Next check:
N/A                | Released: [name]                                                                       |                  |
|                                  |                                   | Valid from: 04.09.2024                                                                                  |                  |

|                   |                          |                                                                 |  |
|-------------------|--------------------------|-----------------------------------------------------------------|--|
| study
protocol | Study: „Soziales Rezept“ | Campus:
CCM                                                  |  |
|                   |                          | Scope:
Institute for General Practice and
Family Medicine |  |

2. monitoring recruitment numbers and loss to follow up ,
3. monitoring compliance with the study protocol by participants and examiners ,
4. monitoring of adverse events,
5. monitoring compliance with previous DSMB recommendations,
6. to consider the ethical implications of all DSMB recommendations.

The DSMB should decide whether to recommend continuing recruitment of participants into the study or to stop recruitment for either all or some treatment groups and/or some subgroups of participants . The DSMB's recommendations are advisory and not executive.

The composition of the DSMB, its working methods (including decision-making) and reporting are defined in the *SocPres\_DSMB Charter* .

## 14 Ethical considerations

The intervention is considered to be low risk for patients because no adverse events were reported in previous studies, although these may not have been adequately recorded.

### 14.1 Individual Benefit

The potential benefit is an improvement in individual health and well-being.

Participants in the intervention group benefit from the opportunity to attend several appointments with a link worker and to use person-centered interaction to find out and articulate their own needs and implement solutions. The support is intended to reduce hurdles and increase the likelihood that participants will be able to take advantage of the services on offer. It is expected that communication with the link worker itself will have an individual therapeutic benefit (motivational interviewing ), but also in particular referral to local services (e.g. through increased social contacts as part of participation in a choir to reduce loneliness or the use of debt counseling for financial problems).

Participants in the control group benefit from the opportunity to communicate their medical and social needs. However, apart from the dissemination of information about local services (" signposting ") so that participants can seek advice or use services themselves, no individual benefit in addition to regular care is to be expected for this group.

|                                  |                                   |                                                                                                         |                  |
|----------------------------------|-----------------------------------|---------------------------------------------------------------------------------------------------------|------------------|
| Version: V1.2                    | Last review:
February 12, 2025 | Created: [name], [name], [name], [name], [name] | Page
43 of 52 |
|                                  |                                   | Reviewed by: [name], [name]                                                    |                  |
| Release on:
February 12, 2025 | Next check:
N/A                | Released: [name]                                                                       |                  |
|                                  |                                   | Valid from: 04.09.2024                                                                                  |                  |

|                |                          |                                                              |  |
|----------------|--------------------------|--------------------------------------------------------------|--|
| study protocol | Study: „Soziales Rezept“ | Campus:
CCM                                               |  |
|                |                          | Scope:
Institute for General Practice and Family Medicine |  |

## 14.2 group benefit

In the long term, the results of the study will serve to improve social and health care for people with non-medical health-related needs. The high-quality, evidence-based results are intended to inform political decision-makers about possible measures to reduce health inequalities and improve health status, well-being and other patient-relevant endpoints. The results may enable the implementation of the social prescription as an integrated care model in regular care. This could mean that the concept could benefit all people with non-medical health-related problems who have access to primary care. It is also potentially possible to expand it outside of primary care (e.g. through pharmacies, emergency rooms, but also municipal services such as the employment agency, the citizens' office or the library). This is already being practiced in other countries.

There is also the potential that the intervention will result in lower use of healthcare, particularly primary care, but also the use of emergency departments. This has the potential to relieve the burden on the healthcare system.

## 14.3 Benefits for participating trial centers

The participating study centers will receive per recruited Patient in an expense allowance of 50 EUR.

## 14.4 damage/risk

For study participants in the control and intervention groups, participation requires a time investment, including for the surveys.

For participants in the intervention group, it is conceivable that the conversations with the link worker could be emotionally upsetting and could therefore lead to decompensation, for example. However, such undesirable effects have not been reported in previous studies and in the widespread implementation in Great Britain. On the contrary, the conversations are seen as more of a relief.

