The secondary objectives of the study include the assessment of acceptability, practicability and need/use of the intervention, as the study is a pilot of social Prescribing in Germany and these parameters are crucial for the design of future offers. The study will also examine the suitability of various endpoints that will be used in the future to determine the health effects of social Prescribing at the individual and health economic level. In addition, adverse events occurring within the study will be systematically recorded in order to make statements about the safety of social Prescribing to be able to meet.

The following table presents the objectives of the study with the associated quantitative endpoints.

|                                  |                                   |                                                                                                         |                  |
|----------------------------------|-----------------------------------|---------------------------------------------------------------------------------------------------------|------------------|
| Version: V1.2                    | Last review:
February 12, 2025 | Created: [name], [name], [name], [name], [name] | Page
16 of 52 |
|                                  |                                   | Reviewed by: [name], [name]                                                    |                  |
| Release on:
February 12, 2025 | Next check:
N/A                | Released: [name]                                                                       |                  |
|                                  |                                   | Valid from: 04.09.2024                                                                                  |                  |

|                |                          |                                                              |  |
|----------------|--------------------------|--------------------------------------------------------------|--|
| study protocol | Study: „Soziales Rezept“ | Campus:
CCM                                               |  |
|                |                          | Scope:
Institute for General Practice and Family Medicine |  |

Table 2: Project objectives and endpoints

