|                |                          | Scope:
Institute for General Practice and Family Medicine |  |

|                         |                                                             |
|-------------------------|-------------------------------------------------------------|
| Determination of Safety | number of deaths among participants                         |
|                         | Number of emergency room visits among participants          |
|                         | Number of unplanned hospitalizations among participants     |
|                         | Number of participants with (newly occurring) suicidality   |
|                         | number of suicide attempts among participants               |
|                         | Number of participants who experienced other adverse events |

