#### 4.5.2 blinding

Due to the study design, blinding of the investigators , link workers and patients is not possible. Due to the 2:1 randomization, blinding of the statistical analyses is also not possible.

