#### 6.1.5 Adverse events

Adverse events are reported by the GP to the study team within seven days. Various secure transmission channels are available for this purpose, which are described in more detail in the associated SOP *SocPres\_SOP Reporting, evaluation and handling of adverse events* . Adverse events are stored in a central database (see Adverse events ).

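### The one clinical harm the protocol foresees, upset leading to decompensation, is not a predefined adverse event, so its milder forms rest on investigator discretion and their count is not a rate

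*Protocol*

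**What the plan says.** Section 3 of the protocol sets the aim: "adverse events occurring within the study will be systematically recorded in order to make statements about the safety". Section 14.4 then names a conceivable clinical harm of the intervention, that "it is conceivable that the conversations with the link worker could be emotionally upsetting and could therefore lead to decompensation". It adds that earlier studies and the British roll-out reported no such effects.

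Section 13.1.1 sets standard adverse-event grading aside and fixes a list: "Instead, the following adverse events are predefined for the study". The list is death, emergency room visit, unplanned hospitalization (each from any cause), suicide attempt or suicidality, and a fifth, open category. That category is explained as follows: "To give investigators the opportunity to report further adverse events that they consider relevant, there is a separate category". Table 2 has the same structure, and its last safety endpoint is "Number of participants who experienced other adverse events".

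On reporting, 6.1.5 states "Adverse events are reported by the GP to the study team within seven days", and 13.1.2 has events sent "via secure communication channels by the investigators to the study management within 7 days of becoming known". Section 4.5.2 notes that "blinding of the investigators , link workers and patients is not possible". Table 4 marks safety at baseline, at every link-worker session and at the three- and six-month interviews. Section 8.4 plans frequencies and percentages of adverse events per arm, and section 16 plans a publication on safety.

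**The concern.** The protocol foresees a specific harm and undertakes to record adverse events systematically, but the list it fixes does not contain that harm. Severe decompensation will usually surface as a listed event. Milder decompensation will not, and its recording then depends on whether an unblinded GP hears of it and judges it relevant.

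The people best placed to notice it are the link workers and the study nurses, and the text gives neither a reporting step. Sessions with a link worker exist in one arm only. If they do act as a safety contact, as Table 4 suggests, that contact is not matched in the control arm.

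At stake is what the safety table and the safety publication can say about this harm. Section 14 itself concedes that earlier studies may not have recorded adverse events adequately. This is a matter of collection: no analysis plan can recover events that nobody asked about or passed on.

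**Working it through.** The protocol gives no rate or precision target for adverse events, so there is no figure of its own to reproduce. The check is mainly a comparison of sections.

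**Where the harm of 14.4 would be recorded**

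| Form of the harm | Route in the text |
|---|---|
| Emergency visit, unplanned admission, death | Predefined in 13.1.1, any cause. Hospital stays and emergency care are also asked about in both arms through the utilization items (6.4, Table 4) |
| Suicide attempt or suicidality, down to passive thoughts | Predefined in 13.1.1 |
| Decompensation or marked distress short of these | Open category only, if the investigator considers it relevant |

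**Who can report it**

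- GP or investigator: stated in 6.1.5 and 13.1.2, in both arms. Section 4.8 keeps GP care unaffected by allocation.
- Link worker: 6.1.7 lists conversation content, offers and duration, with no adverse-event item. The feedback form in 4.3 reaches the GP only after the consultations end, and exists only in the social prescribing arm.
- Study nurse: 4.7.2 to 4.7.4 and 6.1.6 describe the interviews but no safety question.
- Table 4: a safety row at baseline, sessions, three and six months, with no description of what is collected. The adverse-event, data-collection and intervention SOPs are not shown.

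**What a zero count could show at best**

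Inputs from 8.2: 143 and 72 randomized; about 100 and 50 expected at six months (143 × 0.70 = 100.1; 72 × 0.70 = 50.4). The exact two-sided 95% upper limit for zero events is 1 − 0.025^(1/n):

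- n = 143: 2.55%
- n = 72: 4.99%
- n = 100: 3.62%
- n = 50: 7.11%

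The first two limits apply to the harm itself only if every event is captured. If a share c is captured, the limit for the harm is roughly the limit divided by c. The document gives no value for c. The following shares are assumptions, for illustration only:

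| Assumed c | Social prescribing, 0/143 | Control, 0/72 |
|---|---|---|
| 1.00 | 2.5% | 5.0% |
| 0.75 | 3.4% | 6.7% |
| 0.50 | 5.1% | 10.0% |
| 0.25 | 10.2% | 20.0% |

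The table shows that the reading depends on c. It says nothing about what c is, or whether it differs between arms.

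**The case against.** The strongest reply has four parts.

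*The harm is largely covered.* Any-cause emergency visits, any-cause admissions and a broad definition of suicidality take in most serious decompensation, and the open category is itself a Table 2 endpoint. This stands. It would be wrong to infer that the protocol omits the harm; the gap concerns the milder forms.

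*Safety is scheduled at visits.* Table 4 marks it in both arms at baseline, three and six months, and the exact reporting procedure is left to an SOP. This also stands. A reader might infer that the count is known to be unsolicited, but the documents do not support that. They support only that the protocol text does not say what is asked or who passes it on.

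*Reporting is organised and the same in both arms.* There is a form, a seven-day limit, a central listing, a second assessment and regular reports to a safety board. The GP is the stated reporter in both arms. Hence a bias in a known direction cannot be inferred, nor can an outright contradiction of the aim in section 3. But these steps process events once reported; they do not decide whether a mild event is noticed and reported.

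*A distress question would mainly count background distress.* Participants enter with bereavement, violence, housing or legal trouble, and WHO-5 and other scales already track well-being in both arms. This is a good argument for a threshold above everyday distress. It does not remove the need, because scale scores are not event reports and can miss transient upset around a session.

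**Conclusion.** The point holds in a limited form. The harm named in 14.4 is not predefined in 13.1.1 or Table 2. Its forms short of an emergency visit, unplanned admission or suicidality depend on investigator judgement. The text states no reporting step for link workers or study nurses and leaves the Table 4 safety row undescribed. So a low count of this harm, or a difference between arms, cannot be read as its rate.

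The size of any under-count or imbalance cannot be derived from the document. The only firm numbers are the full-capture limits for zero events, 2.5% and 5.0%; wider limits rest on assumed capture shares. The conclusion also assumes that the SOPs add no prompt or reporting route. If they do, what remains is the missing category and a missing cross-reference.

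The point is minor: results are descriptive and exploratory, section 12.2 rates the risk very low, and only statements about safety are affected. It is still worth acting on during data collection, because it cannot be repaired afterwards.

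**What to change.** 1. In 13.1.1 and Table 2, add a predefined event for both arms: psychological crisis or decompensation needing unplanned professional help or contact, or a similar threshold above everyday distress.
2. Ask one identically worded question on it in both arms at the existing three- and six-month interviews, without mentioning the link worker.
3. In 6.1.5 and 13.1.2, state that link workers and study nurses pass any adverse event they learn of to the investigator within seven days, or cite the SOP that already says so. Say what the Table 4 safety row collects.
4. In 8.4, base the between-arm count on the interview question, and list events first noticed in link-worker sessions separately.

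The cost is one line in the list and on the form, plus one question in two interviews already held. Counts will rise in both arms and include background events. Participants already past three months can be asked only at six months, with longer recall, so report by whether the three-month question was asked. The roughly 30% expected not to reach six months stay covered by GP reporting alone after their last interview. Precision stays modest: zero positive answers among the 100 and 50 expected at six months would exclude only rates above 3.6% and 7.1%. The gain is a known denominator and the same question in both arms.
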